## Methods/Design

### Subjects

The study was approved by the research ethics committee of the Hannover Medical School (approval number: 6660). Informed consent will be obtained from the adolescent patients, as well as from their parents. The study cohort will include male and female patients who have undergone a kidney transplant who were between 16 and 22-years-old at study enrollment. There is a huge variation in age at transition in Germany; several centers make the transfer at 18 years whilst others do not transfer until the age of 22. For inclusion the patient must be: at least 14 months away from expected transfer to adult medical care, at least three months post-transplantation, capable of operating a smartphone, and able to provide informed consent. Exclusion criteria are: signs of acute transplant rejection or indications of a need for dialysis in the foreseeable future (since transplant survival is a study outcome variable), as well as mental incapacity (since it may prevent complete and independent use of the apps). Patients will be randomized into two groups: an intervention group that receives case management by the Berliner TransitionsProgramm, which is supported by a smartphone (Samsung Galaxy Y, Samsung, Seoul, South Korea) with two apps; and a control group transferred according to the established protocols of the center. There are centers in Germany which already practice some kind of transition management, however, no center actually uses smartphone apps or case management. Our interventions can also therefore improve outcome in centers that already practice active transition. Because of the center-based stratification used in this study, patients from German centers actually performing transition will be distributed equally amongst both groups.

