### Sample size calculation

We first estimated the likely therapy adherence rate based on a small group of patients on immunosuppressive therapy. Data from Hannover Medical School showed that among six selected patients, three showed very good compliance, with a mean coefficient of variation (%) of 0.13 (±0.03), whereas poor compliance was observed in the three remaining patients, with an average coefficient of variation (%) of 0.5 (±0.03). These values were taken as roughly predictive of the variance we would observe in our study. We will receive additional data from phase I on which to base the sample size assumptions. Assuming a population of 50% with very good compliance, 25% with average compliance, and 25% with poor compliance, we simulated a mixed distribution with the statistical values above and calculated an average coefficient of variation (%) of 0.26, with a standard deviation of 0.15. Our expectation is that the intervention will increase the ratio of patients with good compliance. For that reason we assumed the following positively shifted distribution (%) for the intervention group: 70:30:0 of very good:average:poor compliance. This distribution corresponds to a coefficient of variation (%) of 0.181 with the same standard deviation of 0.15. Assuming a two-sided type I error of 5%, a Student’s two-sample t-test will have 80% power under the planning assumptions if n = 57 patients per group are randomized. Hence, a total of 114 patients must be recruited for this trial. We supposed a negligible dropout rate since it is critical that transplant patients receive ongoing care and attend their treatment centers regularly. In addition, we believe that providing free smartphones will increase adherence. In the unexpected case of too many dropouts, we will extend the recruitment phase to ensure sufficient patients are included in the trial throughout the complete follow-up period.

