### Statistical analysis

The coefficients of variation (%) for immunosuppressive agent levels will be analyzed by analysis of covariance, with adjustment for immunosuppressive agent level at T0 and all stratification variables considered in the randomization, such that the analysis of covariance can be used to determine group differences. [18] Least squares means will be calculated for each group and the difference between the group means will be reported with a two-sided 95% confidence interval (CI). If the upper limit of the CI for the difference between the adjusted means (transition minus standard) for the therapy effect is less than 0, then lower variability in immunosuppressive agent levels and thus better adherence to therapy due to the new transition model is therefore proved. Sensitivity analyses will be carried out using multivariate regression models with consideration of additional prognostic factors (modeling after stepwise variable selection). Secondary dichotomous endpoints (such as transplant loss) will be assessed with multivariate logistic regression models.

All patients included in the study (intention-to-treat population) will be considered in the primary and secondary analyses described above. For patients who suffer a transplant loss, the immunosuppressive agent levels measured before the loss will be used. Using a conservative approach, patients with fewer than three immunosuppressive agent level datum points will be coded with the largest coefficient of variation (%) in their respective therapy group. The study began recruiting patients as from 1 April 2014 (pre-screening).

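### Coding patients who have too few drug levels with the largest CV of their own arm is not reliably conservative: it can exaggerate or shrink the effect, and it inflates the type I error when CVs are skewed.

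*Protocol article*

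**What the plan says.** All of this is in the Protocol article.

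- **Rule (Statistical analysis).** Patients who have fewer than three drug levels "will be coded with the largest coefficient of variation (%) in their respective therapy group", and the section describes this as conservative. The reference group is the patient's own arm, not the whole trial.
- **Population (same section).** "All patients included in the study (intention-to-treat population) will be considered in the primary and secondary analyses described above", so coded patients enter the primary analysis of covariance.
- **Success criterion (same section).** Superiority is declared on this condition: "If the upper limit of the CI for the difference between the adjusted means (transition minus standard) for the therapy effect is less than 0".
- **Planning (Sample size calculation).** Control is assumed to be 50:25:25 very good, average and poor compliers, with mean CV 0.26 and SD 0.15. The intervention arm is assumed to be 70:30:0, with mean 0.181 and the same SD. Very good compliers have a CV of 0.13 (±0.03) and poor compliers 0.5 (±0.03). No CV is given for the average class.
- **Missing data (same section).** Dropout is taken to be negligible. No rate is given for patients with too few levels.

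**The concern.** A worst-value rule is conservative if it pulls the treatment difference towards zero and does not raise the false-positive rate. A rule that takes the worst value from the patient's own arm guarantees neither.

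First, if the intervention works by eliminating poor compliers, its worst observed CV is lower than that of control. A patient with no usable outcome is then coded more favourably for having been randomised to the intervention.

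Second, each arm's most extreme observation is copied to several patients and analysed as if measured. The chance gap between two sample maxima enters the estimate, while the standard error treats the copies as independent data.

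At stake are the size of the primary estimate and the error rate of the primary test.

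**Working it through.** **1. The plan's own figure.** With a difference of 0.26 − 0.181 = 0.079 and SD 0.15, n per arm = 2 × (1.960 + 0.842)² × 0.15² / 0.079² = 56.6, so 57. The stated sample size ("Assuming a two-sided type I error of 5%, a Student’s two-sample t-test will have 80% power under the planning assumptions if n = 57 patients") is reproduced.

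**2. The planning mixtures.** Assume the average class has CV 0.30 with SD 0.03.
- Intervention mean: 0.7 × 0.13 + 0.3 × 0.30 = 0.181, as stated.
- Control mean: 0.5 × 0.13 + 0.25 × 0.30 + 0.25 × 0.50 = 0.265, against the stated 0.26.
- True difference: 0.181 − 0.265 = −0.084.
- SD of the intervention mixture: √(0.03² + 0.7 × 0.3 × 0.17²) = 0.083, not the stated 0.15. The two planning descriptions of this arm therefore differ, and both are examined below.

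**3. Effect on the estimate.** If a fraction p is coded in each arm at random, the expected difference is about

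(1 − p) × true difference + p × (intervention maximum − control maximum).

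The rule moves the estimate away from zero only when the gap between the arm maxima exceeds the true difference.

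*Planning mixtures.* The expected maxima with 57 per arm are about 0.35 and 0.55, a gap of −0.20.
- 5% coded: 0.95 × (−0.084) + 0.05 × (−0.20) = −0.090, which is 7% too large.
- 10% coded: 0.90 × (−0.084) + 0.10 × (−0.20) = −0.096 (simulated −0.095, 13% too large).
- 20% coded: 0.80 × (−0.084) + 0.20 × (−0.20) = −0.107, which is 27% too large.

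Simulated power does not fall (95.6% with none coded, 97.0% at 20%). With one value common to both arms the gap is zero, and the difference becomes −0.080, −0.076 and −0.067.

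*Stated means with equal SD 0.15, lognormal shape assumed.* At 10% coded the expected maxima are about 0.76 and 0.78. The gap of −0.02 is smaller than the true −0.079, so the estimate shrinks: 0.90 × (−0.079) + 0.10 × (−0.02) = −0.073. Simulated power falls from 80% to 70%, 60% and about 51% at 2%, 5% and 10% coded.

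**4. Type I error.** These figures come from simulation: 57 per arm, 40,000 to 60,000 trials per setting, a two-sample t-test standing in for the analysis of covariance, and the same coding probability in both arms, unrelated to outcome. All shapes have mean 0.26 and SD 0.15, except the mixture, which is the control mixture above. The nominal level is 5% two-sided.

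| Shape (assumed) | 2% coded | 5% | 10% | 20% |
|---|---|---|---|---|
| Lognormal | 6.4% | 8.8% | 13.6% | 23.6% |
| Gamma | 6.0% | 7.3% | 10.4% | 17.5% |
| Normal | 5.3% | 6.1% | 7.6% | 10.8% |
| Planning mixture | 5.1% | 5.2% | 5.5% | 5.8% |

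A value common to both arms gives about 5% in every cell.

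**5. Unequal missingness, lognormal, no effect.**
- 10% coded in control and 5% in intervention: about 16% with the own-arm value, 11% with the common value.
- 10% and 2%: about 23% with either.

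**The case against.** The strongest defence is that the rule will rarely be used. Levels are recorded every four to eight weeks in routine care and taken from patient files, so twelve months yields roughly 52/8 = 6 to 52/4 = 13 values. Falling below three should be unusual, and dropout is expected to be negligible. This stands: at 2% coded the type I error is at most about 6.4% in the shapes tabulated. It does not remove the point, since the rule exists for the case where patients are coded. The plan's remedy for excess dropout, a longer recruitment phase, leaves coded patients in the intention-to-treat set.

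A second defence is that the inflation rests on an assumed skewed shape. This also stands. Under the planning mixture it is negligible, and if exactly 3 of 57 are coded in each arm even the lognormal case gives 4.9% (8.3% at 6 of 57).

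A reader might infer that the rule always favours the intervention. The documents do not support that. The 70:30:0 split implies it, but the equal SD of 0.15 stated alongside does not, and the direction also reverses if enough additional patients are coded in the intervention arm.

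A reader might also infer that missingness will differ by arm, because the handset belongs to "an intervention group that receives case management by the Berliner TransitionsProgramm, which is supported by a smartphone" and the plan writes: "In addition, we believe that providing free smartphones will increase adherence". That makes imbalance plausible, but the documents give no figure that shows it.

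**Conclusion.** The point holds in a limited form: own-arm worst-value coding cannot be called conservative. Under the planning mixtures (average class 0.30, SD 0.03 assumed) it exaggerates the difference by about 7%, 13% and 27% at 5%, 10% and 20% coded. Under the stated equal SDs with a lognormal shape it shrinks it. Which happens depends on the upper tails of the two arms and on the balance of missingness. With skewed CVs the type I error rises to about 6%, 9%, 13% and 24% at 2%, 5%, 10% and 20% coded. The documents give neither the CV shape nor a coding rate, so these are ranges under assumptions and not predictions. Adjustment for baseline and strata would change the exact values but not the mechanism.

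It would go too far to say that the primary test is invalid as planned: with few coded patients the distortion is small. The rule should be corrected, but it does not by itself undermine the trial.

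**What to change.** In Statistical analysis, replace "in their respective therapy group" by wording that takes the largest coefficient of variation over both groups, so that the coded value no longer depends on the arm.

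This should not be presented as restoring validity in general. As step 5 of the check shows, a common worst value still gives a biased test when missingness differs by arm. Two additions are therefore needed: a multiple-imputation analysis of the primary endpoint using the stratification factors and baseline data, and a report of the number of coded patients in each arm.

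The cost is one phrase, one further analysis and some power if many patients are coded. Under the planning mixture, power with the common value falls from about 96% to 92%, 85%, 74% and 54% at 2%, 5%, 10% and 20% coded. If dropout is negligible, as the plan assumes, little is lost. The change should be made before outcomes are analysed by arm.

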## Discussion

This study will provide fundamental data about medical care structures in the transition of adolescent nephrology patients from pediatric to adult care. It is designed to test a new transition model using case management and modern telemedicine. According to the interventions used (case management and smartphone apps), our randomized controlled trial is an open unblinded study. This may influence the patient outcomes after 12 and 24 months. However, a blinded design is not possible in this kind of a trial.

To the best of our knowledge, there are no comparable randomized prospective studies in the literature. The major aim of the study is to utilize improved medical care structures, with the long-term goal of improving transplant survival and thereby reducing morbidity and mortality. Upon completion, this study ultimately aims to establish the Berliner TransitionsProgramm, combined with use of apps, as a medical care standard in the transition of young patients who have received a kidney transplant. Once the study has been completed, the apps will be made available throughout Germany. This work has the potential to optimize the medical care of adolescents during the critical pediatric-to-adult care transition phase.

## Trial status

Phase I of the study is in progress. Recruitment has started in November 2014 and is expected to finish in November 2015. The healthcare currently in place is being analyzed and the tools to be used in phase II are being reviewed.

## Abbreviations

CI: Confidence interval
eGFR: Estimated glomerular filtration rate
eCRF: Electronic Case Form
KiO: Kinderhilfe Organtransplantation
KfH: Kuratorium für Dialyse und Nierentransplantation.
